### 11.1.3. Parties Responsible for AE/SAE Reporting

Site investigators and UCSF are responsible for reporting SAEs and related unexpected AEs to all relevant local and US-based IRBs including the UCSF Committee on Human Research (CHR). The following minimum criteria are necessary to trigger expedited reporting of an AE/SAE to these institutions:

- An identifiable patient (Enrollment ID)
- A suspect medicinal product (diaphragm, lubricant gel or male condom)
- An identifiable reporting source (co-PI or designee)
- An event or outcome that can be identified as serious AND unexpected
- A reasonable suspected causal relationship with the investigational product or with study procedures

While the initial SAE expectedness and causality assessments are approved by the site investigator on the original SAE form, the trial’s medical advisor may advise changing the SAE relatedness based on his/her medical review.

Site investigators are responsible for reporting the following to UCSF immediately and to relevant local IRBs no later than ten working days after learning about the event:

- All SAEs that resulted in death or were life-threatening for which expedited reporting is required
- All other SAEs that meet the requirements for expedited reporting
- Unexpected AEs related to study product use

UCSF in turn follows all reporting guidelines of US-based IRBs and informs all other study investigators of the event within 10 working days of being notified by the study site.

## 11.2 Product Interruption and Discontinuation

Active participation in the trial, including use of the diaphragm and/or gel, may be discontinued for any of the following reasons:

- The participant withdraws her consent. Participants may withdraw from study participation at any time, for any reason, without loss of any services to which they may be entitled outside of study participation.
- The participant develops a medical condition that is incompatible with the protocol or the clinician determines it to be in the best interest of the participant to discontinue study product use.
- The participant develops an SAE that may be related to study product use.
- Study staff determine it to be in the best interest of the participant for a non-medical reason.
- UCSF, Ibis Reproductive Health, South African MRC, the University of Zimbabwe, PHRU, the Zimbabwe and South African Ministries of Health, the DSMB, or any relevant IRB or regulatory authority halts the study at one or more site(s).

Women who acquire an STI or a vaginal infection may continue to use the diaphragm and gel. In the event of significant genital ulceration, genital lesions with epithelial disruption, or severe generalized erythema, the participant may also continue to use the diaphragm and gel if she wishes and the clinician agrees. These symptoms are picked up routinely through questions about gynecological symptoms and complaints during regularly scheduled study visits. Re-evaluation visits are scheduled at the discretion of the study clinician until healing or resolution is documented. If the condition does not improve after one or more re-evaluation visits with continued diaphragm and gel use, product use may be interrupted until healing or resolution has been documented. Diaphragm and gel use may then be restarted, if doing so is considered safe by the study clinician. If the condition reappears, permanent discontinuation is considered.

The study clinician, in consultation with the local co-PI and/or another study physician, is responsible for deciding whether temporary or permanent discontinuation of diaphragm and gel use is warranted. Every effort is made to complete all protocol-specified visits and procedures for women whose diaphragm and gel use has been discontinued. Diaphragm and gel use may be restarted at any time, if doing so is considered safe by the study clinician and after consultation with a physician as needed).

Participants are asked to abstain from having sex and using the diaphragm and gel for six weeks post-birth, LEEP, or cryotherapy. Participants are asked to abstain from having sex and using the diaphragm and gel for two weeks after a cervical biopsy, spontaneous abortion, or induced abortion.

## Communicable Disease Reporting Requirements

It is the responsibility of the co-PI of each study site to report communicable diseases identified among study participants to local health authorities as required by local guidelines.

# 12 Data Collection, Management, and Analysis

## 12.1 Identification Numbers

At screening, each woman is assigned a unique identification number, which is separate from the randomization number discussed in Section 8.2. This identification number is entered into the Study Register and written on all screening forms. This identification number is retained for this one woman and used in all subsequent visits for the duration of the trial. Each study site is assigned a range of identification numbers that adequately address the maximum number of screened women.

The Study Register is kept by study staff and contains the name, randomization, and ID number of each participant as well as her contact information for any necessary tracing. This register is kept in a secure environment at the study site, separate from the data collection forms (see Section 13.2). Signed informed consent forms are also be kept locked at the study site, separate from other study forms.

## Case Report Forms

Case Report Forms (CRFs) are used to record all clinical and laboratory information obtained in this trial. As discussed in Section 8.5, all of the self-interview data are collected using ACASI. Source documents include original laboratory reports, study clinician’s notes, counseling forms, and off-site medical records. Medical records may be obtained in the case of SAEs. Completed CRFs and source documents are kept in participant folders in locked files at each study site. One folder is kept per participant. Only study staff, monitors, and auditors or their designees can access these files.

A team of trial investigators at UCSF and Ibis designs the CRFs. Study staff at each site have been trained in how to complete and make corrections to the CRFs. CRFs are completed at the time of participants’ visits in black or blue ballpoint pen. No white-out or other obscuring method is used to correct errors. All corrections to the data is made by drawing a single line through the mistake. All corrections include the date when the change is made and the initials of the person making the change. Staff filling out the CRF check the form for accuracy and completeness. The local study coordinator or designee re-checks each form for completeness and accuracy within the next few days before transmitting and filing them.

Laboratory test results can be reported on forms that are normally used by the laboratories that conduct the tests. In that case, results are transcribed from the source documents onto the relevant study forms at each site.

## 12.3 Translation of Forms

Each study site is responsible for translating the informed consent forms, educational materials, and questions that are directed to participants on relevant CRFs into local language(s). Back-translations into English are completed by a different translator to check the accuracy of the original translations. Back-translations are compared with the original English versions by trial management staff at each site to verify that translations are appropriate. Informed consent forms and educational materials in the local language are submitted to the relevant IRBs. Translations of informed consents are verified by the Project Director at the UZ-UCSF site, by the local IRB at the MRC site, and by translation certificates from a certified company at the PHRU site. Translations, back-translations, and verification documents for informed consents are kept on file at the study site and at UCSF.

## 12.4 Forms Tracking and Storage

All study forms are completed, checked, and filed at each study site and forms will kept at the sites throughout and after completion of the data collection phase for a minimum of five years. *Records may not be destroyed without written permission from UCSF.*

## 12.5 Data Entry and Management

Following each visit, all CRFs are checked at the site for accuracy and completeness. They are then transmitted by email or fax to the Center for International Data Evaluation & Analysis at UCSF where quality control and data management procedures are conducted for all three study sites.

All study participants receive a unique study identification number (ID) that is recorded on all paper forms and in the ACASI system. One electronic file that links participants’ names and study ID numbers per site is maintained by the study coordinator or their designees and is stored on a password protected, secure computer. The file associating names and ID numbers and the ACASI data files is not saved on the same computer.

Paper consent forms, contact information sheets, and other paper data collection instruments are stored in a locked file cabinet located in the project offices at the three study sites. Documents containing personal information, such as consent forms and contact information, are stored separately from study data.

Data from ACASI-based interviews will remain on the password protected computers through the duration of data collection. Daily backups of the ACASI data are done. Copies of the ACASI data are printed at the study sites on a biweekly basis. Print outs of data are signed and dated by the study coordinator and kept in a locked file cabinet. The electronic data is merged once a week and sent to the UCSF data center via email in compressed and encrypted form. ACASI data is converted into SAS (Version 8, SAS, SAS Inc., Cary, NC, USA) to check for cross-visit consistency and to compare ACASI data with associated CRF data.

Incoming CRF data is processed and reviewed using DataFax version 3.7 (Clinical DataFax Systems, Inc.), a commercial software system. This software converts the data on paper CRFs to an exportable database through automatic optical character recognition. 100% of the images of the original CRFs are compared against the database to verify the accuracy of recognized data and to enter data that cannot be recognized electronically. Data is checked for completeness and accuracy, including checks for ranges and skip patterns, by data coordinators using validation tools in DataFax and in SAS. Validated and checked data from clinic visits and ACASI is merged using SAS for additional data integrity checks, the generation of monthly reports on recruitment and follow-up rates, and analysis.

Study data at UCSF is backed up nightly. Backup schemes are based on a five-day weekly schedule. A full backup is performed once a week, with incremental backups on the other days of the week. Weekly tapes with a full backup of the data are stored at a remote location. Monthly tapes will be regularly archived with professional data storage and recovery service in Sacramento, California. Six months of data is maintained at the storage facility.

Information collected on study forms is checked five times: by staff completing the forms at the study visit, by the local study coordinator or designee, by monitors during monitoring visits (see Section 15.3), by data verifiers upon receipt of the images in DataFax, and during data cleaning by UCSF data manager or designee(s). Coding of AEs to specific body systems using the MedDRA coding system is carried out at UCSF by experienced staff that do not have participant contact.

## 12.6 DSMB analyses

The DSMB will review interim data when 100 HIV seroconversions (approximately one-third of the expected 293 infections) have been observed. Based on the advice of the DSMB, an additional interim analysis will be conducted when 195 HIV seroconversions (approximately two-thirds of the expected 293 infections) have been observed. They will tabulate events by study group, site, and woman-years of exposure.

The interim analyses will be performed using an O’Brien Fleming group sequential design. The assumptions used to determine sample size (*i.e.*, accrual, HIV seroincidence, and retention rates at each site) will be assessed and alterations to the overall sample size will be made if recommended by the DSMB. A consulting statistician will develop the DSMB data analysis plan in close collaboration with the co-PIs and data managers of the trial. However, the analyses will be conducted by the consulting statistician and his/her team without involvement of the co-PIs, data managers, any other trial investigators, or any other trial management staff.

The DSMB will also provide clear stopping rules and guidelines for other protocol modifications based on the interim results. The DSMB may also recommend other protocol changes. If interim results provide convincing evidence of safety concerns, significant benefit of diaphragm use, faster accumulation of trial endpoints than anticipated, or futility (*i.e.* a very low probability that the trial will ultimately demonstrate that the diaphragm is effective), the DSMB may recommend early termination of the trial. If interim results suggest that the incidence of trial endpoints is lower than anticipated, but there are no futility concerns, the DSMB may recommend increasing the total woman-years of follow-up. The DSMB may also recommend other protocol changes.

The DSMB report will consist of open and closed sections. The open section will be made widely available, including to all study investigators, who may choose to share the report with IRBs, donors, and other interested parties. This section will include data in aggregate form (*i.e.* not broken down by study arm), focusing on trial conduct issues such as overall accrual and drop-out rates, eligibility rates and reasons for ineligibility, baseline characteristics and condom use, and compliance with protocol procedures, including diaphragm use. The closed sectionof the DSMB report will be made available to DSMB members only. This section will include the above data reported by trial arm and data concerning trial endpoints—such as HIV and STI incidence and rates of adverse events—overall and by trial arms and clinical sites.

## 12.7 Final Data Analysis

The final data analysis of the primary and secondary trial objectives will be a joint process between investigators at UCSF, Ibis Reproductive Health, the Medical Research Council, the University of Zimbabwe, and the Perinatal HIV Research Unit. The four co-PIs in consultation with our TAC, will jointly determine the appropriate data analysis and paper writing processes (see Section 15.5). Fine-tuning of the data analysis plan may take place after the trial begins, but it should be complete by the time the interim analysis is conducted. The data analysis plan will be kept in the regulatory binders at the study sites and at UCSF together with the protocol.

Analyses will be performed on two types of analysis sets: the full analysis set (intent-to-treat analysis) and the per-protocol set (per-protocol analysis). The full analysis set will include all eligible, randomized participants. The per-protocol analysis entails further stratification of the full analysis set based on compliance with the study protocol, most notably diaphragm, gel, and condom use. The precise composition of the per-protocol set will be outlined in the data analysis plan. The intent-to-treat analysis provides the most conservative analysis strategy, with randomization fully intact. A per protocol analysis will also be performed to account for reported study product use (adherence), and not just treatment assignment. Per protocol analyses are generally interpreted as less stringent than ITT analyses because other factors may confound the relationship between study product use and HIV/ STI endpoints.

Any differences in results between the two types of analyses will be explicitly discussed and taken into account in the overall interpretation of trial results. Missing values represent another source of potential bias. While every effort will be made to minimize missing data, the data analysis plan will specify how to handle any missing data.

### 12.7.1 Overall Study Performance

We will calculate accrual, retention and eligibility rates, and describe reasons for ineligibility, other non-enrollment, and discontinuation. We will calculate the number of woman-years of follow-up accumulated in each study arm, the total number of skipped and late visits, and the average follow-up period per woman per study arm. We will calculate the total number of coital acts and diaphragm and condom use during coital acts in a variety of ways. If appropriate, we will test for statistical differences in retention and compliance rates between the study arms using generalized estimating equations. We will test for differences in summary variables using standard t-tests for means and Fisher’s exact test for categorical variables.

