# 2 Study Summary

**Study Purpose:** To determine the effectiveness of the diaphragm with Replens lubricant gel in the reduction or prevention of the heterosexual acquisition of HIV among women.

**Study Design:** Multi-site randomized, controlled, trial with two study arms:

1) Ortho All-Flex Arcing Spring latex diaphragm with Replens lubricant gel, and 2) a non-diaphragm and gel control arm.

Women in both arms receive male condoms, safer-sex counseling, and diagnosis and treatment of sexually transmitted infections.

**Sample Size:** 5,000 women (2,500 per arm) seen for an average of 18 months (range of 12-24 months of follow-up).

**Study Population:** HIV-negative, sexually active, non-pregnant women.

**Visit Schedule:** Screening, enrollment, two-week post-enrollment visit, and 4 to 8 quarterly visits depending on date of enrollment. Optional visits any time for counseling, obtaining additional supplies, or other concerns.

**Study Duration:** Approximately 48 months total, with 6 months for start up activities and 6 months for analysis and write-up.

**Primary Objectives:** To determine the effectiveness of the diaphragm with Replens

lubricant gel in preventing heterosexual transmission of HIV

among at-risk women.

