# 6 Study Population

## Study Sites

(Note that all sites did not begin the study at the same time; site-specific accrual is presented below, section 7.1.2.)

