In April 2005, the study statistician did a recalculation of the sample size based on actual HIV incidence rates to date. The overall annual incidence was found to be 3.5%. In order to maintain 90% power to detect a 33% reduction in HIV infection, it was estimated that 500 more women were needed in the trial, bringing the total sample size to 5000 women. Each site increased their target enrollments: Harare to 2500, Durban to 1500, and Johannesburg to 1000. In addition, re-calculations of the estimated number of infections and woman-years of data needed to detect a difference between study arms have produced higher figures. Thus while previous versions of the MIRA Technical protocol listed 280 incident infections needed, and 3500 woman-years of data per arm, we are now operating under the estimates of 293 incident cases and 4000 woman-years per arm.

The final enrollment numbers for the study sites were 2502 at UZ-UCSF, 1515 at MRC, and 1028 at PHRU. A total of 5045 women were enrolled in the study.

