## Randomization

Ibis Reproductive Health produced a randomization scheme to assign women to one of the two study groups based on a permuted block randomization design based on randomly assigned block sizes of 8, 10 and 12. The randomization scheme is stratified by study site. When each woman enrolls, field staff open the next sealed, opaque, numbered envelope at that site to reveal the study group to which the woman will be assigned. Staff do not open the envelopes until a woman is ready to be enrolled to avoid manipulation of the randomization scheme. Each woman’s group and randomization number are be noted on relevant study forms and in the study register.

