### 12.7.3 Primary Objective and Secondary Objectives 1 & 3: Effectiveness

Cox proportional hazards models, stratified by study site, will be performed to compare the HIV incidence of the diaphragm arm with the incidence in the non-diaphragm control arm. We will consider the diaphragm and gel effective if the HIV infection rate among women randomized to the diaphragm and gel arm is statistically significantly lower than the infection rate among women randomized to the non-diaphragm arm with appropriate adjustment for multiple comparisons and correlated hypothesis tests. Our sample size and power will afford us to have 90% power to detect a relative hazard comparing incidence in women in the diaphragm arm compared to that in the controls of .67 corresponding to an intervention-related reduction of 33% as significantly less than one at the 5% level. Similar analyses will be performed with incident STI infections as secondary endpoints. In the per-protocol analyses, additional co-variates will be included in the hazards models, including frequency of diaphragm, gel, and condom use, and baseline characteristics that were statistically significantly different between the study arms at baseline. We also will conduct analyses, controlling for a number of STIs (*i.e.* TP, HSV-2, and TV), and evaluate these STIs as potential effect modifiers of a diaphragm-HIV relationship. All results will be reported as rate ratios with associated 95% confidence intervals.

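### Section 12.7.1 compares per-woman summary variables between arms with tests that ignore site, although randomisation and the HIV analysis are stratified by site; the likely cost is small.

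*Protocol*

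**What the plan says.** On allocation, section 8.2 (Randomization) uses permuted blocks of 8, 10 and 12 and states: "The randomization scheme is stratified by study site". The Study Summary gives equal arms: "5,000 women (2,500 per arm) seen for an average of 18 months".

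The HIV endpoint follows that design. Section 7.1.1 bases the sample size on a log-rank test stratified by site, and section 12.7.3 says: "Cox proportional hazards models, stratified by study site, will be performed to compare the HIV incidence of the diaphragm arm".

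Section 12.7.1 (Overall Study Performance) first lists quantities to be calculated: woman-years by arm, skipped and late visits, "the average follow-up period per woman per study arm", coital acts, and diaphragm and condom use. It then names two sets of methods:

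- For rates, if appropriate: "we will test for statistical differences in retention and compliance rates between the study arms using generalized estimating equations".
- For the rest: "We will test for differences in summary variables using standard t-tests for means", with Fisher's exact test for categorical variables.

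Neither sentence mentions site.

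**The concern.** When arms are balanced within each site, a site that runs high or low on some variable contributes almost equally to both arms. That between-site variation therefore drops out of the arm difference. A plain t-test estimates its error from the total spread of the data, which still contains that variation. Fisher's exact test likewise pools the sites. Both are then conservative whenever the sites differ on the variable tested.

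There is some reason to expect site differences. Section 6.1 says: "Note that all sites did not begin the study at the same time", a woman's follow-up depends on when she enrolled, and the populations are urban, peri-urban and rural.

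Allocation is visible to participants and staff, so follow-up and behaviour by arm help in reading the HIV result. For that purpose the unwelcome error is to miss a real arm difference, and conservatism makes that slightly more likely.

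**Working it through.** The protocol states no figure for these comparisons, so there is none to reproduce. The check is of direction and size.

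**Inputs from the protocol**
- Equal allocation, in blocks within site (Study Summary; section 8.2).
- Site sizes, section 7.1.1: "The final enrollment numbers for the study sites were 2502 at UZ-UCSF, 1515 at MRC, and 1028 at PHRU". The total is 5045 and the shares are 0.496, 0.300 and 0.204.

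**Inputs assumed**
- Site means, site proportions and within-site SDs. The protocol gives none, so a range is shown.

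**Formula.** Let W be the within-site variance, B the between-site variance and R² = B/(W+B). With balanced blocks, the true variance of the arm difference is about 4W/N, while the plain test uses about 4(W+B)/N. The ratio of plain to site-stratified standard error is

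k = √((W+B)/W) = 1/√(1−R²).

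**Worked example.** Take a yes/no summary at 40/60/80% (Harare/Durban/Johannesburg).
- Overall proportion: 0.496×0.4 + 0.300×0.6 + 0.204×0.8 = 0.542.
- Total variance: 0.542×0.458 = 0.248.
- Within-site variance: 0.496×0.24 + 0.300×0.24 + 0.204×0.16 = 0.224.
- W/(W+B) = 0.901, so k = 1/√0.901 = 1.053.

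**Range of assumptions**

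| Assumed values, Harare/Durban/Johannesburg | R² | k |
|---|---|---|
| Any variable, sites equal | 0 | 1.000 |
| Yes/no summary 95/92/88% | 0.011 | 1.005 |
| Yes/no summary 60/70/80% | 0.028 | 1.014 |
| Yes/no summary 95/90/80% | 0.038 | 1.019 |
| Yes/no summary 40/60/80% | 0.099 | 1.053 |
| Yes/no summary 80/50/30% | 0.173 | 1.099 |
| Mean follow-up 19/18/17 months, SD 3.46 (uniform over 12-24) | 0.049 | 1.025 |
| Mean follow-up 19/18/16 months, SD 6 to 4 | 0.035-0.075 | 1.018-1.040 |
| Mean follow-up 19.5/18/16 months, SD 3.46 | 0.132 | 1.073 |
| Mean follow-up 20/18/15 months, SD 6 to 4 | 0.093-0.187 | 1.050-1.109 |

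**Size and power.** The plain test rejects when the correctly scaled statistic exceeds 1.96k. Its true two-sided size is 2(1−Φ(1.96k)). Its power, where the stratified test has 90%, is Φ(3.2415−1.96k).

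| R² | k | True size | Power (stratified: 90%) |
|---|---|---|---|
| 0 | 1.000 | 0.050 | 0.90 |
| 0.01 | 1.005 | 0.049 | 0.90 |
| 0.05 | 1.026 | 0.044 | 0.89 |
| 0.10 | 1.054 | 0.039 | 0.88 |
| 0.20 | 1.118 | 0.028 | 0.85 |

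Starting from 80% power instead, the formula is Φ(2.80−1.96k). The 40/60/80% case gives 77% and the 19.5/18/16-month case gives 76%.

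**Simulation.** Blocks of 8, 10 and 12, the actual site sizes, SD 5 months, no true arm difference, 1,500 runs per scenario:
- Equal site means: both tests have standard error 0.141 and reject in 5.9% of runs.
- 19/18/16 months: plain standard error 0.144, stratified 0.141, observed SD of the difference 0.141. Rejection 4.7% plain, 5.7% stratified.
- 20/18/15 months: plain standard error 0.151, stratified 0.141, observed SD 0.142. Rejection 3.2% plain, 4.8% stratified.

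The simulation error on a 5% rejection rate is √(0.05×0.95/1500) = 0.6 percentage points, so the pattern agrees with the formula.

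**The case against.** - **Which comparisons are covered.** A reader might infer that all arm comparisons of visit completion and condom use go to plain tests. The text does not support that. Retention and compliance rates go to GEE, and section 12.7 describes compliance chiefly as diaphragm, gel and condom use. The term summary variables is not defined. Reading it as per-woman quantities such as average follow-up, visit totals and use summaries is natural, because these are listed just before, but it is a reading. The yes/no rows above apply only to variables handled as categorical summaries. Diaphragm and gel are supplied to one arm, so condom use is the main product comparison between arms. This objection stands and limits the point.
- **Site differences are not shown.** Start dates do not rank the sites cleanly. Harare opened in September 2003, but its Epworth area opened only in March 2004, the same month as Johannesburg. Follow-up is also capped at 24 months. This stands: every size is conditional.
- **The absolute effect is tiny.** With 5045 women, the 40/60/80% case has standard errors of √(4×0.248/5045) = 1.40 and √(4×0.224/5045) = 1.33 percentage points. The 19.5/18/16-month case has about 0.105 and 0.098 months, a gap of about 0.2 days. The tests stay valid, with size at or below 5%. This also stands.
- **It is analysis-plan detail.** Section 12.7 defers detail to a separate data analysis plan. That answers the unstated GEE covariates, which are no fault in the protocol. It does not fully answer the t-test and Fisher's test, because the protocol names those tests itself and they do not follow its own randomisation strata.

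**Conclusion.** The point holds in a narrow form, as a minor improvement. The tests named in section 12.7.1 for summary variables do not use the strata within which women were randomised, whereas the HIV analysis does. If sites differ on those variables, the standard errors are too large in expectation and the tests conservative. On assumed site values the excess is nil with no site differences, roughly 0.5-5% for moderate ones and about 10% for large ones. The loss is at most a few points of power.

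Two stronger readings should be resisted. A reader might infer that the error bars are too wide as a matter of fact, but section 12.7.1 specifies no intervals and the excess depends on site differences that the protocol does not report. A reader might also infer that the main safeguard on the HIV result is impaired. The HIV model is already stratified by site and is not affected, and section 12.7.3 brings diaphragm, gel and condom use into the per-protocol hazards models.

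**What to change.** Amend the last two sentences of section 12.7.1:

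- Compare means of per-woman summaries with a linear model containing arm and site, in place of the standard t-test.
- Compare categorical summaries with a site-stratified Cochran-Mantel-Haenszel test, or an exact stratified test where counts are small, in place of Fisher's exact test.
- State that the GEE models for retention and compliance include site, so that all the arm comparisons in the section treat site alike.

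No new data are needed and the HIV analysis does not change. The only cost is slightly more programming.
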